### Ethical considerations and dissemination

This study will strictly adhere to the ethical principles outlined in the Declaration of Helsinki [World Medical Association Declaration of Helsinki, 2008]. The research protocol has been granted approval by the Ethics Committee Nove de Julho University with protocol number 6.080. 655.Any modifications to the protocol will be promptly communicated to this same committee and duly updated on ClinicalTrials.gov.

Participants will be comprehensively briefed on all potential risks associated with their involvement in the study, as well as the stringent confidentiality measures in place for their data.

The data collected during the research will be stored and organized in the Harvard Dataverse repository [https://dataverse.harvard.edu]. Metadata will be published on the repository’s website through the provided platform link [DOI]. Participant-related data and research outcomes will remain confidential. Only the researchers will have access to this information. After the research is concluded, the data will be published and disseminated in national and international scientific events and journals. Raw data will remain on the platform and, after publication, may be made available to other researchers upon contact with the responsible researcher and under a confidentiality and intellectual property agreement.

### Patient and public involvement

Eligible individuals will receive comprehensive explanations about the study’s aims and procedures. They will provide consent, which will be both written and verbally confirmed. Patients will not participate in recruitment or trial implementation. After data analysis, volunteers may attend a meeting to receive the results. Any potential difficulties arising from the interventions will be evaluated by the patients. The confidentiality of all individuals will be safeguarded throughout the research process. Participants will be allowed to withdraw from the study at any time.

### Expected results

It is expected that we will ascertain whether there is a difference between the effects of vascular and local photobiomodulation on orofacial pain, with the study’s aim to develop and validate a dosimetric model for individualized protocols based on the unique characteristics of each patient.

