**Methods:**

The objective of this project is to validate a dosimetry model based on the relationship between the effects of photobiomodulation with anthropometric and hemodynamic variables, both in local application and systemic application in patients with symptoms of orofacial pain and tension headache. For this purpose, 180 participants with orofacial pain post-covid eligible participants will be randomly assigned to Group 1—Local Photobiomodulation, Group 2—Vascular Photobiomodulation, Group 3—Placebo Local Photobiomodulation, or Group 4—Placebo Vascular Photobiomodulation [Therapy EC–DMC device, São Carlos, Brazil,– 660 nm, 100mW] using stratified block randomization. Before the application, sociodemographic information such as age, skin phototype [classified by the Fitzpatrick scale], weight, height, body mass index [BMI], oxygen saturation [SaO2], blood pressure [BP], heart rate [HR], and thickness of skin, fat, and facial muscles will be collected. During the application, we will collect local temperature, SaO2, BP, and HR. Before and after laser application, blood levels of lactate and hemoglobin, BP, and HR will be measured in the first and last session. In addition to demographic, anthropometric, and hemodynamic variables, the penetrated energy will be quantified using a power meter, and information from orofacial pain and headache symptom questionnaires will be analyzed. The Monte Carlo simulation technique will be used to systematically study the relationship between the light penetration profile into the target tissues and the most relevant variables, namely BMI, tissue layer thicknesses, and skin phototype. Light transmittance, measured in vivo and simulated, will be compared to validate a personalized dosimetry model.

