### Interventions

#### Group 1 –Local photobiomodulation

The treatment will be administered over 2 weeks, totaling 4 sessions [2 sessions per week] with an average duration of 6 minutes per session.

Participants will be positioned in a clinical chair for the application of photobiomodulation. The interventions will be conducted by a trained professional. Group 1 will receive photobiomodulation using the Therapy EC–DMC device, with a red wavelength of 660 nm and power of 100 mW, properly calibrated, delivering 6J per point [60 seconds] at 2 points in the masseter muscle region, 1 point in the left temporal muscle,1 point in the right temporal muscle, 1 point in the left trapezius muscle in the cervical region, 1 point in the right trapezius muscle. The total application time will be 4 minutes per session.

At the time of application, only the participant receiving the treatment, the researcher responsible for the treatment, and the guardian will be present. Everyone will wear specific goggles for eye protection. The equipment’s tip will be disinfected with 70% alcohol and covered with disposable transparent plastic [PVC] to prevent cross-contamination, while the facial area to be irradiated will be cleaned with a 0.2% Chlorhexidine solution. During the applications, the participant will remain seated, with the Frankfurt plane parallel to the ground. Energy penetration will be analyzed at one of the points on the masseter muscle.

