#### Group 2 –Vascular photobiomodulation

Vascular Photobiomodulation [VBMP] will be applied using the same device, with an infra-red wavelength of 808 nm and 100 mW, directing the light beam to the radial artery region for 10 minutes per session.

The participant will be seated in a comfortable chair with lateral support for resting their arms during the application. At the time of application, only the participant receiving the treatment, the researcher responsible for the treatment, and the guardian will be present. Everyone will wear specific goggles for eye protection. The active part of the bracelet will be covered with disposable transparent plastic [PVC] to prevent cross-contamination, and for hygiene reasons, the area to be irradiated will be pre-cleaned with a 0.2% Chlorhexidine solution. During the applications, the participant will remain seated, with the Frankfurt plane parallel to the ground. A new treatment method will be administered for 2 weeks, totaling 4 sessions [2 sessions per week] with an average duration of 10 minutes per session.

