**Fig 1 pone.0309073.g001:**
[figure not shown]
The SPIRIT schedule of enrolment, interventions, and assessments.

**Table 1 pone.0309073.t001:** Dosimetric parameters for photobiomodulation application.

PARAMETERS	RED LASER [Local]	INFRARED LASER [Transcutaneous Systemic]
Wavelength [nm]	660	808
Mode	Contínuo	Contínuo
Power [mW]	100	100
Aperture Diameter [cm]	0,354 [beam diameter with spacer]	0,354 cm
Beam Area [cm^2^]	0,0984 [with spacer]	0,0984 cm^2^
Exposure Time [s]	60 per point	600 s
Fluence [J/cm^2^]	61	-
Energy [J]	6 per point	60 J
Number of irradiated points	6	Systemic
Application Technique	Contact	Contact
Number of sessions	4	4
Treatment Frequency	2 times per week	2 times per week
Total Irradiated Energy [J]	144 J	240 J

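### The local-versus-vascular comparison is one between two complete regimens and cannot isolate route; the abstract also gives one wavelength where the body gives two

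*Protocol article*

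**What the plan says.** The section Expected results says the investigators expect to "ascertain whether there is a difference between the effects of vascular and local photobiomodulation on orofacial pain". The section Study variables names orofacial pain as the primary outcome.

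The two active regimens are defined in their own sections and set side by side in Table 1:

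- **Group 1 (local)** is treated "with a red wavelength of 660 nm and power of 100 mW", "delivering 6J per point [60 seconds] at 2 points in the masseter muscle region", with four further points on the temporal and trapezius muscles. Table 1 counts six points and 144 J in total. The section describes sessions "with an average duration of 6 minutes per session" and, in its next paragraph, says "The total application time will be 4 minutes per session".
- **Group 2 (vascular)** is treated with the same device, "with an infra-red wavelength of 808 nm and 100 mW", over the radial artery region for 10 minutes. Table 1 gives 60 J per session and 240 J in total. In place of a point count it enters Systemic.

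Groups 3 and 4 repeat the procedures of Groups 1 and 2 without laser emission. The abstract lists all four groups and then gives a single device setting: "Therapy EC–DMC device, São Carlos, Brazil,– 660 nm, 100mW".

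**The concern.** The expected result names the two treatments by route alone. If pain falls more in one active group than in the other, the natural summary is that one route works better. The design cannot support that, because wavelength, total energy, sites and session time all change together with route.

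This matters more here than in most trials. The study is about dosimetry, and its introduction explains that varying energy, power and wavelength across earlier trials prevented an ideal protocol from being derived. Those same quantities differ between the arms being compared. A reader of the abstract alone would think that wavelength had been held constant.

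There is a second, separate issue. One procedure is done on the face and neck and the other on the wrist, and participants can see which they receive. A direct contrast of the two active groups would include any difference in placebo response between the procedures. The matched sham groups can remove that part, but the sentence under Expected results does not say whether they are used.

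**Working it through.** **1. Reproduce the energies in Table 1** (energy = power × time, power 100 mW = 0.1 W).

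- Local: 0.1 × 60 = 6 J per point; × 6 points = 36 J per session; × 4 sessions = 144 J. This matches.
- Vascular: 0.1 × 600 = 60 J per session; × 4 sessions = 240 J. This matches.

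**2. Set the two active regimens side by side.**

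| | Local (Group 1) | Vascular (Group 2) | Same? |
|---|---|---|---|
| Wavelength | 660 nm | 808 nm | no |
| Total energy | 144 J | 240 J | no; ratio 240/144 = 1.67 |
| Sites | 6 points, face and neck | radial artery region | no |
| Session time | 6 min (also 4 min) | 10 min | no; ratio 1.67 (or 2.5) |
| Power | 100 mW | 100 mW | yes |
| Sessions | 4, twice weekly | 4, twice weekly | yes |

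The only other groups are the two shams, which emit no light. No group gives the local route at 808 nm or the vascular route at 660 nm, and none equalises energy. The effects of route, wavelength and energy are therefore not separately estimable.

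**3. Check the two session times for Group 1.** Six points × 60 s = 360 s = 6 min, which agrees with 144 J. Four minutes at 100 mW would be 0.1 × 240 = 24 J per session, or 96 J over 4 sessions, which disagrees with Table 1. This shows only that the statements are inconsistent, not which one is intended.

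**4. Precision of the two possible contrasts.** The sample of 180 at 1:1:1:1 gives 45 per group. In SD units, assuming equal variance and all participants analysed:

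- Direct, G1−G2: SE = √(2/45) = 0.211.
- Through the shams, (G1−G3)−(G2−G4): SE = √(4/45) = 0.298.
- Ratio: √2 = 1.41.
- Difference detectable with 80% power at two-sided 5%, as (1.960 + 0.842) × SE: about 0.59 SD direct and 0.84 SD through the shams.

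The section Discontinuation or interruption criteria removes some participants from analysis, so 45 is an upper limit and the real SEs would be somewhat larger.

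**5. Illustration of placebo-response bias in a direct test.** The documents give no figure for a gap in placebo response between the procedures, so a range is assumed. With no true difference between the regimens, the rejection probability is Φ(−1.96 + g/0.211) + Φ(−1.96 − g/0.211):

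| Assumed gap g | Direct test rejects |
|---|---|
| 0.1 SD | about 8% |
| 0.2 SD | about 16% |
| 0.3 SD | about 30% |

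The contrast through the shams stays at 5% in all three cases if the placebo response in each sham group equals that in its active counterpart.

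**The case against.** The strongest reply is that the article never claims to isolate route. Local and vascular photobiomodulation are the names of Groups 1 and 2, each defined as a complete regimen, and Table 1 displays their differences openly. A randomised comparison of two packages is valid. This stands: a reader might infer from Expected results that a difference will be attributed to route, but the text does not say so. What remains is that the sentence does not limit its interpretation either.

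A reader might also infer that a direct Group 1 versus Group 2 test is planned, with an inflated false-positive rate. The documents do not support this. They specify no such contrast, they speak of effects, and the Discussion refers to placebo controls when describing how those effects are evaluated. The choice of contrast may also sit in an analysis plan that is not shown. The percentages in step 5 are therefore an illustration of why the shams should be used, not a property of the plan.

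It would likewise be too strong to say that the abstract hides the difference in wavelength. The Group 2 section and Table 1 both state 808 nm, and the Monte Carlo section models both wavelengths. The abstract is nevertheless in conflict with them.

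Two further points stand. Differing sites are partly inherent to the route, so wavelength and total energy are the clearest separable confounders. And the main stated aim is validation of a dosimetry model, so this comparison is one part of the study. Neither point removes the confounding, and no analysis plan could.

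**Conclusion.** The point holds as a limit on interpretation together with two textual contradictions.

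- **Wrong as written:** the abstract's single wavelength against the Group 2 section and Table 1, and the 6-minute and 4-minute statements in the Group 1 section.
- **Limit on interpretation:** route is fully confounded with wavelength (660 vs 808 nm) and total energy (ratio 1.67), as well as with sites and session time. The comparison is valid only between two regimens. This follows from the listed arms and needs no assumption.
- **Cheap improvement:** using the matched shams guards against a difference in placebo response. The size of that risk rests on assumed gaps and on a direct test that the article does not specify.

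A reader might expect the contrast through the shams to solve the attribution problem. It does not: it removes the placebo component and leaves wavelength and energy confounded with route.

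**What to change.** 1. In Expected results, state that the comparison is between two complete regimens, each defined by its column in Table 1, and that a difference will not be attributed to route. Cost: one sentence.
2. If a vascular-versus-local difference is estimated, define it as (G1−G3)−(G2−G4), report it with its confidence interval, and label it secondary. Cost: a standard error 1.41 times that of a direct contrast, so only differences of about 0.84 SD or more would be detected with 80% power at 45 per group. No extra participants or procedures are needed.
3. Reconcile the wavelength in the abstract with the Group 2 section and Table 1, and reconcile the two session times in the Group 1 section with each other and with the energy in Table 1. Which values are intended is for the investigators to state. Cost: a correction to the text.

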## Discussion

The present study addresses a significant gap in the understanding of optimal dosimetry for photobiomodulation therapy in patients experiencing orofacial pain and tension headache post-Covid-19. The introduction of low-level laser therapy [LLLT] as a potential alternative for pain management underscores the importance of determining precise dosimetric parameters tailored to individual patient characteristics. This study’s objective to validate a dosimetry model based on anthropometric and hemodynamic variables is crucial for optimizing treatment efficacy and minimizing potential adverse effects associated with pharmacological interventions [9, 10].

An essential aspect of this research lies in its methodological approach, which involves a randomized assignment of participants to different treatment groups, including placebo controls. Such a design ensures rigorous evaluation of the effects of both local and systemic photobiomodulation therapies, thereby enhancing the reliability and validity of the findings. Furthermore, the comprehensive data collection process, encompassing demographic, anthropometric, and hemodynamic variables, as well as measurements of skin and tissue characteristics, enables a thorough investigation of the factors influencing treatment outcomes.

The study’s incorporation of Monte Carlo simulation represents a novel and sophisticated analytical technique for elucidating the relationship between light penetration profiles and key variables, such as BMI and tissue layer thicknesses. By systematically exploring these associations, the research aims to develop a personalized dosimetry model, thereby advancing the precision and effectiveness of photobiomodulation therapy.

The discussion also highlights the potential implications of the study findings for clinical practice, particularly in the context of managing orofacial pain in post-Covid-19 patients. Given the growing recognition of the long-term effects of Covid-19 on various physiological systems, including pain perception and modulation, the validation of a dosimetry model tailored to this population is of paramount importance.

Moreover, the collaborative nature of the study, involving multiple centers across different regions, reflects a concerted effort to address a pressing clinical need in a global context. The prompt ethical approval and enthusiastic participation from the vascular community underscore the study’s relevance and potential impact on improving patient care.

In conclusion, the study’s methodological rigor, innovative approach, and clinical relevance position it as a significant contribution to the field of photobiomodulation therapy. By elucidating the optimal dosimetry parameters for pain management in post-Covid-19 patients, the research has the potential to enhance treatment outcomes and alleviate the burden of orofacial pain and tension headache in this population.
